## **3.4 Variables and biometric methods**

### **3.4.1 Outcome variables**

**Primary Endpoint:** Rate of dry eye symptoms defined by OSDI  $\geq 13$  at 3 months

**Secondary Endpoints:** Rate of DED defined by OSDI  $\geq 13$  plus at least one of the following:

Presence of ocular surface staining, TFBUT  $< 10$ s at 1 week, 1 and 3 months

Comparison of dry eye related parameters between the groups: TFBUT, Staining scores (modified Oxford Grading Scale) at 1 week, 1 and 3 months

Change of dry eye related parameters during the study period (baseline, 1 week, 1 and 3 months) in the study eye: TFBUT, Staining scores (modified Oxford Grading Scale)

Change of OSDI score during the study period (baseline, 1 week, and 3 months)

**Exploratory Endpoints:** Comparison of dry eye symptoms rate DED rate between Group 1, Group 2 and Group 3, BCVA, IOP, Concomitant medication and Adverse Events

### **3.4.2 Biometric methods**

#### **3.4.2.1 Data handling procedures**

A case report form will be completed for each patient.

#### **3.4.2.2 Biometric methods - outcome variables**

For statistical analysis SPSS (Version 25.0) will be used. For missing data, observations will be excluded from analysis.

Descriptive data will be shown as mean, standard deviation and range. Difference in dry eye related parameters (TFBUT, Meibomian gland expressibility and staining scores) will be compared between the groups using unpaired t-tests. ANOVA for repeated measures is used to investigate changes of dry eye related parameters and OSDI Score between the study visits. Tukeys post-hoc analysis will be used for group wise comparison.

Die deskriptiven Daten werden als Mittelwert, Standardabweichung und Bereich angegeben. Die Unterschiede in den Parametern des trockenen Auges (TFBUT, Meibom-Drüsen-Expressibilität und Staining-Scores) werden zwischen den Gruppen mittels ungepaarter t-Tests verglichen. Die ANOVA für wiederholte Messungen wird verwendet, um die Veränderungen der Parameter des trockenen Auges und des OSDI-Scores zwischen den Studienbesuchen zu untersuchen. Tukeys Post-hoc-Analyse wird für den gruppenweisen Vergleich verwendet.

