### **OBJECTIVES:**

The aim of this study is to compare the signs and symptoms of dry eye after cataract surgery between groups, patients with preoperatively high risk and low risk, and evaluate if adequate and frequently administered lubrication eye drops reduce the signs and symptoms of dry eye in patients with high risk compared to standard of care. The following 3 groups will be compared:

- **Group 1, high risk: Standard of care** OSFI  $\geq 0,3$ , NSAID (2x day for 4 weeks)
- **Group 2, high risk: Treatment** OSFI  $\geq 0,3$ , Systane Hydration MDPF eye drops (4 x day for 3 months) NSAID (2x day for 4 weeks)
- **Group 3, low risk: Reference** OSFI  $< 0,3$ , NSAID (2x day for 4 weeks)
  - **Primary objective:** To compare the rate of dry eye symptoms between Group 1 and Group 2 at 3 months (after cataract surgery)
  - **Secondary objective:** To compare the rate of dry eye symptoms between Group 1 and Group 2 at 1 week and 1 month after cataract surgery. To compare the rate of dry eye disease (DED, Signs and symptoms) between Group 1 and Group 2 at 1 week, 1 and 3 months after cataract surgery.
- Vergleich der Rate der Symptome des trockenen Auges zwischen Gruppe 1 und Gruppe 2 1 Woche und 1 Monat nach der Kataraktoperation. Vergleich der Rate der Erkrankung des trockenen Auges (DED, Anzeichen und Symptome) zwischen Gruppe 1 und Gruppe 2 1 Woche, 1 und 3 Monate nach der Kataraktoperation.

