#### **3.2.1 Number of subjects**

For sample size calculation we used the data published earlier by Villani et al.[1] In the study 50% of the patients with an OSFI score higher than 0.3 (high risk group) developed dry during the study period. The rate was 9.6% in the group with an OSFI score lower than 0.3. These two proportions were used to calculate the sample size. We assume a clinical benefit of the lubrication drops if the rate of occurrence of dry eye in the high-risk group is reduced close to the value of the low-risk group (15%).

Using an alpha error of 0.05 and a power of 80 % we need to include 27 in group 1 and group 2. Due to the long study period, we expect a dropout rate of 30%. Therefore, we need to include 39 patients in group 1 and group 2. 39 patients will be included in group 3.

In total 117 patients will be enrolled into the study.

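### Excluding missing observations while expecting 30% dropout leaves the primary 3-month comparison to completers, which can bias it if dropout depends on symptoms differently in the two groups.

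*Protocol*

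**What the plan says.** Protocol section 3.4.2.2 (Biometric methods - outcome variables) states: "For missing data, observations will be excluded from analysis". It makes no exception for the primary endpoint. The protocol names no analysis population, imputation or sensitivity analysis.

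The primary objective is "To compare the rate of dry eye symptoms between Group 1 and Group 2 at 3 months". Section 3.4.1 defines the outcome as OSDI of 13 or more at that visit, so a patient without the visit contributes nothing to the primary comparison.

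Section 3.2.1 gives the size: "Using an alpha error of 0.05 and a power of 80 % we need to include 27 in group 1 and group 2". It continues: "Due to the long study period, we expect a dropout rate of 30"%, and "Therefore, we need to include 39 patients in group 1 and group 2".

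Section 5 schedules OSDI at screening, baseline, 1 week, 1 month and 3 months. Section 3.3.1.4 asks patients to use no eye drops beyond their assigned routine and offers rescue medication for significant dry eye complaints. Section 3.3.1.5 requires withdrawal for use of forbidden medication. It does not say whether rescue medication is forbidden, or whether withdrawn patients are still followed to 3 months.

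**The concern.** Raising enrolment from 27 to 39 restores the number of completers. It does not make them representative of those randomised. If patients who leave Group 1 differ in symptoms from those who leave Group 2, the completer comparison no longer estimates the randomised contrast.

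Three features of the design make this plausible:

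- Masking covers the observer only, and Group 1 has no comparator drop, so patients know their group.
- The endpoint is a patient-reported questionnaire.
- A patient with symptoms who self-treats may have to be withdrawn, and Group 1, without lubricant, is the more exposed group.

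At stake are the size of the primary effect, the power to detect it and, in some patterns, the false-positive rate. Earlier OSDI scores from the same patients would go unused for the 3-month comparison.

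**Working it through.** **The plan's own figures.** Inputs from section 3.2.1: 50% in Group 1, 15% in Group 2, alpha 0.05 (taken as two-sided), power 80%, equal groups, 30% dropout.

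- n = [1.96·√(2·0.325·0.675) + 0.8416·√(0.5·0.5 + 0.15·0.85)]² / 0.35² = 26.9, so 27 per group. The normal-approximation power at 27 is 80.2%.
- 27/0.7 = 38.6, so 39. Both figures reproduce.
- Expected exclusions: 39 × 0.30 = 11.7, about 12 per group, or 24 of the 78 randomised.

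**Outcome-related dropout when there is a true effect.** The dropout patterns here and below are assumptions, because the protocol gives only the total. Let p be the true rate, d_s the dropout among symptomatic patients and d_a the dropout among the others. The observed completer rate is p(1−d_s) / [p(1−d_s) + (1−p)(1−d_a)].

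Each pattern is applied to Group 1 only and keeps its overall dropout at 30% (for example 0.5·0.40 + 0.5·0.20 = 0.30). Group 2 dropout is unrelated to symptoms. Power is the exact binomial sum for the uncorrected chi-square test with 27 per group.

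| Group 1 dropout, symptomatic / other | Group 1 observed | Group 2 observed | Power |
|---|---|---|---|
| 30% / 30% | 50% | 15% | 82% |
| 40% / 20% | 0.30/0.70 = 43% | 15% | 65% |
| 45% / 15% | 0.275/0.70 = 39% | 15% | 55% |

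**No true effect (50% in both groups).** Simulation of 39 enrolled per group, 40,000 trials per pattern, pooled z test among completers:

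| Dropout pattern | Two-sided error | Mean difference, Group 1 − Group 2 |
|---|---|---|
| 30% / 30% in both groups | 5.0% | 0 |
| 45% / 15% in Group 1 only | 13.0% | −10.7 points |
| 45% / 15% in Group 2 only | 12.5% | +10.7 points |
| 45% / 15% in both groups | 5.3% | 0 |

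Direction matters. When symptomatic patients leave Group 1, nearly all the excess errors go against the drops: 0.3% of trials falsely favour them. When symptomatic patients leave Group 2, 12.2% of trials falsely favour the drops.

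**Same pattern in both groups with a true effect.** At 40%/20% in both groups the observed rates are 42.9% and 11.7%. The odds ratio is (0.429/0.571)/(0.117/0.883) = 5.67, the same as (0.50/0.50)/(0.15/0.85) = 5.67. The difference in rates narrows from 35 to 31 points.

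**How fragile would a planned-size result be?** Take 14/27 against 4/27 among completers (p = 0.004), with 12 missing in each group.

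- Under the 40%/20% pattern, 0.20/0.30 = 67% of those missing from Group 1 are symptomatic, about 8 of 12. Significance is then lost only if at least 10 of the 12 missing in Group 2 are events (22/39 against 14/39). Group 2 completers have a rate of 15%.
- A reversed sign needs 0 of 12 events in Group 1 and at least 11 of 12 in Group 2 (14/39 against 15/39), or 1 and 12 (15/39 against 16/39).

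**The case against.** The strongest reply is that the 30% is a planning allowance attributed to study length, not a forecast of symptom-driven loss. Randomisation is at screening, and surgical complications are an exclusion criterion that would trigger withdrawal, so some losses may have nothing to do with dry eye. Rescue medication also gives symptomatic patients a reason to stay. All of this stands: the documents show no differential dropout, and every magnitude above is assumed.

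It is also true that complete-case analysis does not fail merely because dropout is related to symptoms. If the relation is the same in both groups, the test keeps its level under no effect and the odds ratio is unchanged. The mechanism that comes first to mind, symptomatic Group 1 patients leaving, shrinks the apparent benefit and does not create one.

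A reader might infer that the direction of the primary result hangs on the missing patients. The documents do not support that: as shown above, reversal needs near-worst-case assumptions. A significant result can be made non-significant, for example 16/39 against 10/39 (p = 0.15), but this supposes 2 of 12 events among Group 1's missing and 6 of 12 among Group 2's. That runs opposite to the mechanism feared and is an extreme case.

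Two points about the remedy also stand. Entry requires OSDI below 14, so baseline OSDI has a narrow range and may predict little for patients lost early. Imputation assumes missing at random, so by itself it does not remove bias from dropout that depends on unseen 3-month symptoms.

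The reply that this belongs in a statistical analysis plan does not stand. The protocol fixes the exclusion rule, and a later plan would have to depart from it. Nor are the earlier scores lost altogether: the 1-week and 1-month OSDI serve secondary objectives. They are unused only for the primary 3-month comparison.

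**Conclusion.** The concern holds as a possible bias, not a demonstrated one. The stated rule would remove about 31% of the randomised high-risk patients (24 of 78) from the primary comparison at the planned dropout, and the enlarged enrolment does not correct any selection this causes.

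The bias requires dropout that depends on symptoms differently in the two groups. Under the assumed patterns, power falls from 82% to between 55% and 65%, or the type I error rises from 5% to about 13%. If dropout is unrelated to outcome, neither happens. The figures assume two-sided alpha of 0.05, an uncorrected comparison of two proportions, the protocol's 50% and 15% (50% in both groups for the type I error), and 30% overall dropout.

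This is an inexpensive improvement to a stated rule. It does not show that the planned analysis must give a wrong answer.

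**What to change.** For the primary endpoint, replace the exclusion sentence in section 3.4.2.2 with the following:

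- **Primary analysis:** all randomised Group 1 and Group 2 patients, using the OSDI scores from screening, baseline and, where attended, 1 week and 1 month. Either impute the 3-month OSDI by multiple imputation and dichotomise it at 13 after imputation, or fit a repeated-measures binary model. Put group in the imputation model and keep the predictor set small, because only about 27 completers per group are expected.
- **Tipping-point analysis:** vary the event rate among missing patients separately in each group, and report where the conclusion changes.
- **Sensitivity analysis:** retain the complete-case result.

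Sections 3.3.1.4 and 3.3.1.5 must also be reconciled on whether rescue medication leads to withdrawal, since that determines who has missing data.

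The cost is protocol wording and a little more analysis. There are no new visits or data, and 27 and 39 per group stand. The primary analysis will rely on missing at random, and the tipping-point analysis tests that reliance. The change should be made before outcome data are seen.

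### For change in OSDI score, the only stated group comparison is a three-group Tukey test that, in its usual form, averages over visits including baseline and so dilutes a lubricant effect

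*Protocol*

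**What the plan says.** Protocol section 2, under the objectives, says that the trial is to "evaluate if adequate and frequently administered lubrication eye drops reduce the signs and symptoms of dry eye in patients with high risk", compared with standard of care. That is a Group 2 versus Group 1 question.

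Section 3.4.1 lists as a secondary endpoint "Change of OSDI score during the study period (baseline, 1 week, and 3 months"). It lists change in TFBUT and staining separately, over four time points.

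Section 3.4.2.2 provides three tools:

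- Unpaired t-tests between groups for TFBUT, meibomian gland expressibility and staining. OSDI is not in this list.
- For the course over time, a model that does include OSDI: "ANOVA for repeated measures is used to investigate changes of dry eye related parameters and OSDI Score between the study visits".
- For comparing the three groups, one further sentence: "Tukeys post-hoc analysis will be used for group wise comparison".

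The German text in the same section says the same. For the continuous OSDI score, the last two sentences are the whole stated method. Neither mentions a group-by-visit contrast, a between-group difference in change, or adjustment for baseline.

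**The concern.** The treatment question for a change endpoint is whether Groups 1 and 2 change equally from baseline. Neither stated step, used in its ordinary form, tests that.

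- **Visit test.** Its null is no change over time. Every patient has cataract surgery between baseline and the first follow-up, so surgery alone can reject it whether or not the drops work.
- **Tukey on the group factor.** In a repeated-measures ANOVA, this compares each patient's mean over visits. One of those visits is baseline, before any drop is given (section 3.3.1.4 starts the drops after surgery), when the randomised groups cannot differ through treatment. The family also contains two contrasts with Group 3, which is defined by low OSFI and not randomised, and this tightens the threshold for the one randomised contrast.

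Two misreadings then become possible. A significant visit effect could be taken as benefit, or a non-significant averaged Tukey test could be reported as no group difference in OSDI when a late benefit exists.

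**Working it through.** **The plan's own figure.** Section 3.2.1 states "Using an alpha error of 0.05 and a power of 80 % we need to include 27 in group 1 and group 2". With rates of 50% and 15%, two-sided alpha 0.05, 80% power, pooled variance and no continuity correction:

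n = [1.960·√(2·0.325·0.675) + 0.842·√(0.5·0.5 + 0.15·0.85)]² / 0.35² = 26.9, so 27 per group.

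27/0.7 = 38.6, so 39 per group, and 3 × 39 = 117. The figure reproduces. It concerns the primary endpoint and is not in question. The protocol gives no power for OSDI change; I take 27 completers per group from here.

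**Dilution, with no assumption on SD or correlation.** The averaged effect is the sum of the effects at each visit divided by the number of visits k, with zero at baseline.

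| Effect after surgery | 3 visits as listed for OSDI | 4 visits as scheduled |
|---|---|---|
| Constant from week 1 | 2/3 = 67% | 3/4 = 75% |
| Growing (0, half, full) | – | 1.5/4 = 38% |
| Only at 3 months | 1/3 = 33% | 1/4 = 25% |

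The four-visit column is shown because the schedule in section 5 collects OSDI at 1 month too.

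**Power, under assumptions.** These are not in the documents: full effect 0.8 SD, SD 1 at every visit, equal correlation ρ between visits, normal data, nothing missing. Power comes from the noncentral t with noncentrality Δ/√(2V/27), where:

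- averaged means: Δ = averaged effect, V = [1 + (k−1)ρ]/k;
- change from baseline to 3 months: Δ = 0.8, V = 2(1−ρ);
- 3 months adjusted for baseline (ANCOVA): Δ = 0.8, V = 1−ρ².

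For three groups of 27 (78 df) the studentized range value is 3.379, so the Tukey threshold is t = 3.379/√2 = 2.389. That is a per-comparison level of 1.9%. Worked case, three visits, constant effect, ρ = 0.5: Δ = 0.533, V = 0.667, noncentrality 0.533/√(2·0.667/27) = 2.40, power 51%.

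The averaged cells give power at the Tukey threshold, then at an unadjusted 5%, so that averaging and multiplicity can be told apart.

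| Contrast, Group 1 v 2 | ρ = 0.3 | ρ = 0.5 | ρ = 0.7 |
|---|---|---|---|
| Averaged, 3 visits, constant | 62% / 75% | 51% / 65% | 43% / 58% |
| Averaged, 3 visits, 3 months only | 15% / 26% | 12% / 22% | 10% / 19% |
| Averaged, 4 visits, constant | 79% / 88% | 66% / 78% | 55% / 69% |
| Averaged, 4 visits, growing | 22% / 35% | 17% / 28% | 13% / 23% |
| Averaged, 4 visits, 3 months only | 10% / 18% | 8% / 15% | 7% / 13% |
| Change at 3 months, 5% | 68% | 82% | 96% |
| Baseline-adjusted at 3 months, 5% | 86% | 91% | 98% |

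**Visit test.** In a simulation with ρ = 0.5, no lubricant effect and an assumed surgery-related shift of 0, 0.5, 0.3 and 0.2 SD over the four visits in all groups, the visit test rejects in 97% of trials. The Group 1 v 2 contrast of change rejects in 5%.

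**The case against.** The strongest reply is that the protocol under-specifies rather than specifies a wrong test. Nowhere does it say that Tukey compares means averaged over visits. It does not list the model's factors or exclude the interaction, which a two-factor repeated-measures ANOVA normally reports, and such detail is often left to an SAP. This stands as a limit: the averaging is inferred from how the method ordinarily works. It does not remove the point, because section 3.4.2.2 chose and named a group comparison, and its ordinary form answers a different question.

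Second, the OSDI endpoint is worded as change over the study period, with no group contrast. That is true. The group purpose comes from the objectives and from the group-wise sentence itself. Nor does the protocol treat a visit effect as evidence for the drops, so the 97% figure shows a risk of misreading, not a declared error.

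Third, part of the power gap is multiplicity. With 5% on both, the constant four-visit case at ρ = 0.5 is 78% against 82% for change, and at ρ = 0.3 averaging beats unadjusted change (88% v 68%). This also stands. A reader might infer that the plan will largely miss a lubricant effect on OSDI. The documents do not support this in general: it holds for late or growing effects, and the time course is unknown.

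A reader might also infer that the trial's main symptom question is compromised. It is not: the primary endpoint is a rate at 3 months, and TFBUT and staining have their own between-group t-tests at each postoperative visit.

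**Conclusion.** The point holds in limited form. For continuous OSDI change, the stated tools are a visit test that surgery alone can make significant and a three-group Tukey comparison that, in its usual form, averages in a visit with no possible treatment effect. The certain part, given that form, is the dilution: a constant effect loses 25% to 33% of its size and an effect present only at 3 months loses 67% to 75%.

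The power consequence depends on assumed values. At 0.8 SD and ρ = 0.5, Tukey on averaged means has 8% to 17% power for late or growing effects and 51% to 66% for a constant one, against 91% for a baseline-adjusted comparison at 3 months. At ρ = 0.3 with an immediate, sustained effect over four visits, the loss is small (79% v 86%) and is due to Tukey's threshold, not to averaging. Equal variances are a further simplification, since entry requires OSDI below 14 and may narrow the baseline spread.

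Only secondary change endpoints are touched. The change is worth making because the better contrast is nearly free.

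**What to change.** In section 3.4.2.2, replace the Tukey sentence, as far as the treatment comparison is concerned, with wording such as:

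*For OSDI score, and for change in TFBUT and staining, the treatment comparison is the Group 2 versus Group 1 difference at 3 months adjusted for the baseline value (ANCOVA, or the group-by-visit contrast in the repeated-measures model), with estimate and 95% CI; 1 week and 1 month are supportive. The visit main effect is descriptive. Comparisons with Group 3 are exploratory and may keep Tukey.*

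One of the two forms should be chosen in advance. They are not identical: a plain group-by-visit contrast from baseline to 3 months is the unadjusted change comparison (82% at ρ = 0.5), while ANCOVA gives 91%.

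The cost is one paragraph. No new patients, visits, measurements or software are needed, and the 3-month focus matches the primary endpoint. There are two small downsides. Group 1 v 2 is tested at 5% instead of about 2%. And if the effect is immediate and sustained with low correlation, averaging over visits can be about as powerful (88% v 86% at ρ = 0.3, four visits, both at 5%).

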#### **3.4.2.3 Biometric methods - Adverse events/Safety investigations**

All adverse events will be properly listed, and an appropriate method will be used to summarise the data. Visual acuity, intraocular pressure and anterior segment findings (such as inflammatory reactions) are documented during each study visit.

#### **3.4.2.4 Use of study findings**

The findings of this study will be published by the investigators in a scientific journal (JCRS) and presented at scientific meetings (Austrian national congress 2022, DOG 2022, ESCRS 2022).

## **4 Methods of evaluation**

---

### **4.1 Best-corrected visual acuity**

Best corrected visual acuity will be assessed using ETDRS charts.

### **4.2 Ocular surface disease index – OSDI**

The OSDI Questionnaire is a standardized questionnaire to evaluate the subjective disease burden caused by dry eye syndrome. The patients answer up to 12 questions regarding their symptoms. Thereafter, the OSDI Score is calculated.

### **4.3 Photography of the anterior segment**

Three photographs of the anterior segment of the eye will be taken. One centered on the cornea (with and without fluoresceine) and one on the upper and the lower eyelid respectively. Images will be used to document changes on the ocular surface and eye lid margin.

#### 4.4 OSFI Score from Villani et al.[1]

Table 4. Final Ocular Surface Frailty Index Composition

| Item                                                | Results                                                        | Points     |
|-----------------------------------------------------|----------------------------------------------------------------|------------|
| Connective tissue diseases                          | No                                                             | 0          |
|                                                     | Yes                                                            | 1          |
| Thyroid malfunction                                 | No                                                             | 0          |
|                                                     | Yes                                                            | 1          |
| Psychiatric conditions*                             | No                                                             | 0          |
|                                                     | Yes                                                            | 1          |
| Computer use †                           | No                                                             | 0          |
|                                                     | Yes                                                            | 1          |
| Ocular allergy                                      | No                                                             | 0          |
|                                                     | Yes                                                            | 1          |
| History of refractive surgery                       | No                                                             | 0          |
|                                                     | Yes                                                            | 1          |
| Topical drugs ‡                          | No                                                             | 0          |
|                                                     | Yes                                                            | 1          |
| TBUT with fluorescein (sec)                         | ≥10 s                                                          | 0          |
|                                                     | 5-9 s                                                          | 0.50       |
|                                                     | 0-4 s                                                          | 1          |
| Meibomian gland expressibility (digital expression) | Grade 0: clear meibum easily expressed                         | 0          |
|                                                     | Grade 1: cloudy meibum expressed with mild pressure            | 0.33       |
|                                                     | Grade 2: cloudy meibum expressed with moderate pressure        | 0.66       |
|                                                     | Grade 3: meibum not expressed with more than moderate pressure | 1          |
| LIPCOF                                              | Grade 0                                                        | 0 points   |
|                                                     | Grade 1                                                        | 0.33 point |
|                                                     | Grade 2                                                        | 0.66 point |
|                                                     | Grade 3                                                        | 1 point    |

BAK = Benzalkonium chloride; LIPCOF = lid parallel conjunctival folds; TBUT = tear film breakup time.

\*Including affective disorders, somatoform disorders, anxiety, and depression.

†Exposure >4 hours/day.

‡Current use of at least 1 of the following topical drugs: antiglaucomatous, antiallergic, antiviral, decongestants, miotics, mydriatics, nonsteroidal anti-inflammatory, or at least 3 drops/day BAK preserved.

